### Preference

2.9

Preference for either shoe condition will be captured at the end of the trial for each participant. A REDCap survey will be created to ask participants which shoe condition (minimalist or balance‐enhancing) was preferred or if there was no preference.

### Evaluation of Adherence

2.10

Adherence will be assessed using the Orthotimer temperature sensor. The Orthotimer system is a valid and reliable instrument, which objectively measures adherence to wearable devices including orthoses and footwear [41]. The sensor will be embedded into both types of shoe styles (minimalist and balance‐enhancing) in locations imperceptible to participants. According to the manufacturer, the sensor has quartz‐controlled time measurement at 32,768 kHz frequency and a temperature precision of ± 0.1°C. The sensor dimension is 9 × 13 × 4.5 mm. Each participant will be allocated one Orthotimer sensor and it will be placed in the shoe (minimalist or balance‐enhancing) that the participant is allocated to at that timepoint. The sensors will be placed into shoes prior to the shoes being issued to participants, and the data will be collected during each 6‐week period. The Orthotimer sensors will be set to capture data at 20‐min intervals.

### Adverse Events

2.11

Adverse events will be reported as the number of participants experiencing any adverse event (serious or nonserious), the number and types of adverse events and the number of withdrawals because of adverse events. Adverse events will be documented at weeks 6 and 12 via a REDCap survey [42]. Participants will be asked to document the type of adverse event, the body location and the severity of the effect. Serious adverse events will be defined as events that are life‐threatening, require hospitalisation or result in persistent or significant disability or incapacity [43]. Participants experiencing a serious adverse event (e.g., significant pain) will be asked to contact one of the investigators and further management will be implemented as appropriate.

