### Statistical Analysis

2.14

Statistical analysis will be performed using the most recent version of SPSS (IBM Corp., Armonk, NY, USA) available at the time of analysis. Analysis will adhere to the intention‐to‐treat principle for all randomised participants. Standard tests to assess continuous data for normal distribution will be used and transformation carried out if required. The primary outcome will be averaged data from 5 questions from the MOSQ [13]. Analysis will be performed using a repeated measures analysis of variance. Four effects are worthy of consideration: (i) the treatment effect, (ii) the order effect, (iii) the treatment‐order interaction effect and (iv) the carry‐over effect [46]. The treatment effect is the direct effect of minimalist versus balance‐enhancing shoes. The order effect implies that the sequence in which treatments are given influences the outcome. The treatment‐order interaction effect implies that the effect of the treatment is influenced by the order in which it is presented. Finally, the carry‐over effect refers to the effect of the previous treatment on the next treatment. In our study, we consider the carry‐over effect to be negligible, as the outcome measures are specific to the shoe being worn. Multiple imputation will be used to replace any missing data using 5 iterations, with baseline scores and order as predictors. Frequency of adverse events will be compared using relative risk and risk difference statistics.

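### Section 2.11 gives significant pain as an example of a serious adverse event, but pain alone does not meet the definition in the sentence before it

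*Protocol article*

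**What the plan says.** Section 2.11 (Adverse Events) of the protocol article contains the definition: "Serious adverse events will be defined as events that are life‐threatening, require hospitalisation or result in persistent or significant disability or incapacity". The sentence that follows gives an example and attaches an action to it: "Participants experiencing a serious adverse event (e.g., significant pain) will be asked to contact one of the investigators".

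The same section lists what will be reported. The first item is "the number of participants experiencing any adverse event (serious or nonserious", followed by the number and types of events and the withdrawals they cause. On data capture it says: "Adverse events will be documented at weeks 6 and 12 via a REDCap survey". On content it says: "Participants will be asked to document the type of adverse event, the body location and the severity of the effect".

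Section 2.14 (Statistical Analysis) has one sentence on the subject: "Frequency of adverse events will be compared using relative risk and risk difference statistics".

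**The concern.** The definition rests on what an event threatens or leads to. The example describes how strong a symptom is. Severity and seriousness are separate attributes of an adverse event, and here the second sentence uses one to illustrate the other. Staff coding events by the definition and staff coding by the example would label the same report differently.

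The label also has a practical use, because the request to contact an investigator is addressed to participants with a serious event. If the label is unclear, so is the group to whom the request applies.

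The example is not a remote case. Section 2.6 asks women to wear new shoes outdoors as often as they can, and one of the two pairs has an insole with firm 3 mm projections. Pain is a foreseeable complaint in such a trial.

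**Working it through.** The document gives no adverse event rate, count or threshold, so there is no figure to reproduce. The check compares the two rules and then follows the label to each place where it could be used.

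**Step 1: apply each rule to the possible cases.**

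| Event | By the definition | By the example |
|---|---|---|
| Significant pain that is life-threatening or leads to hospital admission | Serious | Serious |
| Significant pain that leaves lasting or substantial disability or incapacity | Serious | Serious |
| Significant pain with none of these consequences | Nonserious | Serious |

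The rules disagree only in the third row. The example carries no qualifier that would restrict it to the first two rows. The nearest part of the definition is "require hospitalisation or result in persistent or significant disability or incapacity", which concerns the result of an event and not the intensity of a symptom.

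**Step 2: look for text that settles the matter.** Nothing else in the article does so. Table 1 lists adverse events at the two follow-up visits without mentioning seriousness. The survey items named in section 2.11 are type, body location and severity, and the sentence names no seriousness criterion.

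**Step 3: see which stated outputs depend on the label.**

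- Participants with any adverse event: unchanged. The item covers both classes, so moving an event from one to the other leaves the total the same.
- Number and types of events: unchanged.
- Withdrawals because of adverse events: unchanged.
- Relative risk and risk difference in section 2.14: unchanged, because they compare overall frequency.
- Any breakdown by seriousness: would change, but the article does not state that one is planned.
- Who is asked to contact an investigator: depends on the label, so the third row is covered or not according to the sentence followed.

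The primary outcome, the sample size and the power do not involve the label.

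**The case against.** The strongest reply is that the consequences are small and the conflict is one of loose wording. Pain can be bad enough to stop a woman walking, and pain of that degree could amount to substantial incapacity. On that view the example is shorthand for a case that does meet the definition. This reading is possible, but the text does not state the qualifier, so the example as printed still reaches further than the definition.

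The reply is right about three stronger inferences that a reader might draw:

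- **That the planned safety results would be distorted, for instance a serious-event count for each shoe.** The article commits to no such count. Its reporting item pools the two classes, and section 2.14 compares overall frequency.
- **That a woman in significant pain has no reason to call and could wait as long as 6 weeks for the next survey.** The sentence that asks for contact itself names significant pain. Read as written, it asks her to call. The delay arises only if she applies the formal definition and ignores the example.
- **That the contact request is the only route by which an event is heard of between surveys.** This is an argument from silence. The article is a condensed account, and the full protocol and the participant information sheet are not shown.

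What survives the reply is the inconsistency itself. Both sentences are current, complete and adjacent, so neither condensation nor text extraction accounts for it.

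**Conclusion.** The point holds as an internal inconsistency in section 2.11. Significant pain without any of the defining consequences is nonserious by the definition and serious by the example. Any classification by seriousness, and the set of participants to whom the contact request applies, are therefore not fixed by the text.

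Its size is modest. No analysis stated in the article changes, and the number of events involved cannot be estimated because no rate is given. The conclusion assumes that the printed wording reflects the operative rule. An unseen participant sheet or full protocol may word it more clearly, but the published text would still contradict itself. This review takes no position on which rule is clinically right.

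**What to change.** Reconcile the two sentences in section 2.11 so that one definition of serious governs both the classification and the example given for it. In the same edit, make clear which events the request to contact an investigator covers. Which events those should be is for the investigators to decide.

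The cost is a rewording of two sentences, plus a check that operational documents, if they repeat the wording, agree with it. No visit, measurement or analysis changes. Section 3.1 says recruitment has begun, so an early correction would give more participants the same instruction.

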### Data Management

2.12

Enrolment, baseline and follow‐up questionnaire data will be stored in REDCap and subsequently stored as electronic files on the La Trobe University secure server.

### Sample Size

2.13

In crossover trials, each participant acts as their own control, which greatly reduces between‐participant variability and therefore reduces the required sample size. In the absence of a widely used primary outcome measure, we averaged data from five questions from the MOSQ [13] used in our recent pilot study [11]. These questions are related to participant perceptions of the attractiveness (to both self and others), comfort, fit and ease of donning and doffing of minimalist shoes versus balance‐enhancing shoes, scored on a 0 to 100 visual analogue scale. Using the crossover trial formula described by Jones and Kenward [44], a mean difference of 12.5, standard deviation of 27.8, power of 0.80 and alpha level of 0.05, we determined that a total of 39 participants would be required. This equates to an effect size of 0.45, which is considered a medium effect size using the thresholds proposed by Sawilowsky [45]. Our key secondary outcome measure, the FES‐I [34], has a mean difference of 8.0, and standard deviation of 15.6 when comparing participants with a low and high concern about falling. Using the same formula, we determined that a total of 30 participants would be required, which equates to a medium effect size of 0.51 [45]. To account for an estimated 10% attrition rate, we will recruit an additional 5 participants. Therefore, we will recruit 44 participants to address the sample size requirements for both our primary and key secondary outcome measures.

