### Outcome Measures

2.8

The primary outcome measure is footwear acceptability [13], which will be measured using a modified Monitor Orthopaedic Shoes Questionnaire (MOSQ) at weeks 6 and 12, which allows participants to have 6 weeks in each shoe condition. The MOSQ consists of seven items which address attractiveness to self, attractiveness to others, comfort, fit, ease of donning and doffing, weight satisfaction and perceived durability. All items are scored on a 100‐point VAS. Each of the 7 MOSQ items will be reported separately, but our primary outcome will be calculated from the average score of the 7 items (attractiveness to self, attractiveness to others, comfort, fit, ease of donning and doffing, weight and durability).

Secondary outcome measures will be perceived risk of falling using the Falls Efficacy Scale International (FES‐I) [34] and balance performance (upper body stability when walking, using the validated GyKo sensor) [35, 36], both measured at weeks 6 and 12. The FES‐I is a widely accepted tool to assess an individual's concern about falling [37], which asks about 16 activities and uses a 4‐point Likert scale with the following options: not at all concerned, somewhat concerned, fairly concerned and very concerned. The minimum score is 16 (no concern about falling) and the maximum score is 64 (severe concern about falling). Both the MOSQ and FES‐I will be administered as surveys using REDCap.

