There are several limitations of this trial. First, the inability to blind both the participants and researchers administering the interventions may introduce performance bias; however, this is a commonly recognised limitation in trials which employ nonpharmacologic interventions [47]. Second, our trial is restricted to women only. This is due to the balance‐enhancing footwear being available only in women's styles and sizing; thus, the results of the trial will not necessarily be generalisable to men. Third, a related issue is that participants will be recruited from a single University Podiatry Clinic. Although the clinic is open to the public and anyone can receive podiatric care, our sample may not be broadly generalisable. Fourth, risk of falls was not included as part of the eligibility criteria for either study, meaning the study sample may include participants at relatively low risk of falls. This decision was intentional and pragmatic as both the footwear conditions are retail products that are commercially available, and the balance‐enhancing shoes are not specifically marketed to older women at elevated risk of falls. Fifth, the MOSQ was developed and validated for footwear acceptability of orthopaedic shoes specifically and includes further measures specific to prosthetics and orthotics. We have opted to use a modified version of this tool as there is currently no tool available for evaluating acceptability of nonorthopaedic, commercial footwear. Lastly, due to the nature of the trial and the interventions we are employing, there may be concerns surrounding the aesthetics of both shoe conditions (minimalist or balance‐enhancing). If participants dislike the design of either shoe condition, this may be a deterrent for intervention adherence.

Findings from the trial will provide much needed data regarding footwear acceptability and balance performance in older women. The results of this trial may be used to inform the design of new footwear promoting better adherence to wearing footwear that may reduce the risk of falls in older people. A qualitative study will also be conducted after the completion of this trial which will focus on the lived experience of women aged 65 years or older who have worn balance‐enhancing shoes.

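### The FES-I sample size rests on a gap between people with low and high concern about falling, not on a within-person difference between shoes, so the claim that 44 participants meet its requirement is unsupported

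*Protocol article*

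**What the plan says.** Section 2.13 (Sample Size) of the protocol article makes two calculations.

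- **Primary outcome (MOSQ).** The inputs are "a mean difference of 12.5, standard deviation of 27.8". They come from pilot answers about the two shoe types, on attractiveness and "comfort, fit and ease of donning and doffing of minimalist shoes versus balance"-enhancing shoes. With "power of 0.80 and alpha level of 0.05, we determined that a total of 39 participants would be required".
- **Key secondary outcome (FES-I).** The article says that it "has a mean difference of 8.0, and standard deviation of 15.6 when comparing participants with a low and high concern about falling". It continues: "Using the same formula, we determined that a total of 30 participants would be required, which equates to a medium effect size of 0.51".

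Five participants are added for 10% attrition, and the section ends: "we will recruit 44 participants to address the sample size requirements for both our primary and key secondary outcome measures".

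Sections 2.2 (Design) and 2.14 (Statistical Analysis) define what the trial estimates. Each woman wears both shoes, in AB or BA order, and the treatment effect is the contrast between minimalist and balance-enhancing shoes.

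**The concern.** A two-period crossover calculation takes two inputs: the difference between treatments, within the same person, that the trial should detect, and the SD of those within-person differences. By the article's own description, the FES-I figures are something else. The 8.0 is a gap between people who are more and less concerned about falling, and the 15.6 is the SD attached to that comparison. How far two kinds of people differ does not tell us how far one woman's score moves when she changes shoes, or how variable that movement is.

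The MOSQ inputs at least compare the two shoe types. No passage makes the same link for the FES-I. The article does not argue that 8.0 is a difference worth detecting between shoes, and it gives no within-person SD or correlation.

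At stake is how the FES-I result may be read. The article calls this the key secondary outcome and says that its sample size requirement is addressed. A reader could then take a null FES-I result as coming from an adequately sized comparison, which the stated inputs cannot support.

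**Working it through.** **Inputs from Section 2.13:** FES-I difference 8.0, SD 15.6; power 0.80; alpha 0.05; required number for the primary outcome 39; attrition 10%. Assumed, because not stated: two-sided alpha and equal allocation to the two orders.

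**Step 1. Reproduce the plan's figure.** With the SD read as the SD of within-person differences,

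N = (z₀.₉₇₅ + z₀.₈₀)² × (SD/δ)² = (1.960 + 0.842)² × (15.6/8.0)² = 29.8, rounded up to 30.

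Effect size = 8.0/15.6 = 0.51. Both stated figures reproduce. A t-based version with n − 2 degrees of freedom gives 32. Other readings do not give 30: a per-period SD with zero correlation gives 60, and a parallel-group design gives 60 per arm. So 15.6 was used as the SD of within-person differences.

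**Step 2. What that use implies.** If 15.6 is a between-person SD, equal in both periods, then

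SD of differences = 15.6 × √(2(1 − ρ)),

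where ρ is the within-person correlation. This equals 15.6 only when 2(1 − ρ) = 1, that is ρ = 0.5. The article states no ρ.

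**Step 3. What 39 completers can detect.** With a two-sided 0.05 test, 80% power and 37 degrees of freedom, the detectable difference at SD 15.6 is 7.19 points. As a multiple of the SD of differences, this is 7.19/15.6 = 0.461. The values of ρ below are illustrative.

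| ρ (assumed) | SD of differences | Detectable with 39 (0.461 × SD) | N needed for 8 points |
|---|---|---|---|
| 0 | 22.06 | 10.2 | 62 |
| 0.3 | 18.46 | 8.5 | 44 |
| 0.5 | 15.60 | 7.2 | 32 |
| 0.7 | 12.08 | 5.6 | 21 |
| 0.8 | 9.87 | 4.6 | 15 |
| 0.9 | 6.98 | 3.2 | 9 |

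**Step 4. Sensitivity to the target difference.** Keeping 15.6 as the SD of differences, 39 completers give 88% power for a true difference of 8 points. For 6, 5, 4 and 3 points (illustrative) power is 65%, 50%, 34% and 22%.

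**Step 5. Effect on the total.** 39/0.9 = 43.3, rounded up to 44. The primary outcome alone produces the recruitment target.

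**The case against.** The strongest reply has three parts.

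*The calculation is correct and changes nothing in the design.* Both statements are true. The figure of 30 reproduces, so the fault lies in the inputs, not the arithmetic. Deleting the FES-I sentences would leave recruitment, primary power and the analysis as they are. That limits the weight of the point, but the article still makes an explicit adequacy claim that its inputs do not support.

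*A sample size may target a difference worth detecting; it need not predict the effect.* This is also right, and 8.0 could in principle be such a target. The article does not argue that, however. It gives the low-versus-high-concern comparison as the source, and that is no rationale for a shoe effect.

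*The error may run in the plan's favour.* This stands. At correlations of 0.8 to 0.9 the SD of differences would be about 7 to 10, and 39 completers could detect about 3 to 5 points.

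A reader might also argue that 8 points is out of reach, because the scale has a floor ("The minimum score is 16 (no concern about falling") and the Discussion says that "the study sample may include participants at relatively low risk of falls". The documents do not support this. The contrast is shoe against shoe on a scale from 16 to 64, so one shoe may raise the score while the other lowers it. For example, means of 19 and 27 differ by 8, and neither is at the floor. The Discussion remark concerns risk of falling, whereas the FES-I measures concern about falling, and the article gives no expected FES-I mean.

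**Conclusion.** The point holds as one of wrong inputs. The FES-I requirement of 30 is computed correctly for a quantity that the trial does not estimate, so the statement that 44 participants address the key secondary outcome's requirement is unsupported.

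A reader might go further and infer that the FES-I comparison is underpowered. The documents do not show that. They give neither a between-shoe target nor a within-person SD, so no corrected N can be computed and the direction of the error is unknown. Across assumed correlations of 0 to 0.9, and with 15.6 taken as a between-person SD, the difference detectable with 39 completers runs from about 10 points down to about 3. What can be stated without those assumptions is the standardised figure: about 0.46 SD of within-person differences at 80% power, given a two-sided 0.05 test and 39 completers.

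The finding does not touch the total of 44 or the power for the primary outcome.

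**What to change.** In Section 2.13:

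1. Remove the FES-I requirement of 30 with its inputs, and remove the word 'both' from the closing sentence.
2. State that the primary outcome alone sets the sample size.
3. State that 39 completers give 80% power (two-sided 0.05) for an FES-I difference of about 0.46 SD of within-person differences. Do not present assumed SDs as facts; the table above is illustration and need not go into the protocol.
4. Report the FES-I as an estimated between-shoe difference with a 95% confidence interval, and do not describe it as powered.

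Alternatively, keep an FES-I calculation but justify a target difference between shoes and a within-person SD or correlation, then recompute.

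The first route costs a few reworded sentences, and the claim made for the FES-I becomes less favourable. The second route needs a source for both inputs and could give a number above or below 44. The first route leaves recruitment and primary power unchanged.
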